
#### Moderators of uptake and patient reported outcomes (aim 3a)

Moderators are collected at baseline and include sociodemographics, health literacy, comfort with technology and general health status. Sociodemographic data includes race/ethnicity, education, marital status, gender, age, zip code, health insurance status, usual source of care status, employment status, financial wellness [130] and household income. Test result, including cancer versus cardiovascular/other actionable result and the specific gene are recorded. General health status [129] and personal and family history of cancer and cardiovascular disease are included in the baseline survey. Health literacy is assessed at baseline (T0) with 3 items validated to detect inadequate health literacy in clinical medical populations [131]. Comfort with technology is assessed with selected items from the NCI Health Information National Trends Survey (HINTS), including internet and social media use electronic medical record use and perceptions of privacy (7 items) [132].

Additionally, individual use of digital interventions are recorded throughout the study to evaluate the impact of intervention usage (e.g. dosage) on outcomes and who benefit from supplemental digital education or digital-ROR.

#### Multi-stakeholder mixed-methods process evaluation (aim 3b)

CFIR-informed constructs have been selected to evaluate factors related to uptake of our digital delivery model, and implementation facilitators, barriers and adaptations. We will collect additional quantitative and qualitative data from multiple key informants participating and not participating in the study. Proposed key informants include biobank participants, GCs, medical providers, including genetic specialists and PCPs, and research and clinical support staff. Other proposed key informants not participating in the study include other research teams, health system administrations, information technology staff, and insurers. Sources for our mixed methods process evaluation will include participant surveys, research meeting notes and records and key informant interviews as outlined in Supplemental Table 1.

### Data analysis plan

#### Primary non-inferiority analyses

We hypothesize that disclosure of actionable results by digital-ROR, with access to a GC, can provide non-inferior short-term and longitudinal cognitive, affective, and behavioral outcomes, and lower costs. Primary effectiveness outcomes include: post-disclosure knowledge and cancer or cardio disease-specific distress. We will test whether the receipt of results differ between arms as a secondary analysis. Receipt of results is considered a health behavior. For the 2 primary analyses, we will apply non-inferiority tests to examine if access to digital-ROR is non-inferior to GC disclosure. We will conclude non-inferiority if the upper bound of the randomization effect 97.5% one-sided confidence interval [CI] for cross-sectional T1 responses do not cross a -0.45 standardized difference threshold (i.e., margin) for knowledge and a 0.2 standardized threshold (i.e., margin) for disease-specific distress in the direction that would suggest that digital-ROR is worse. A standardized difference is the difference after variables are scaled to have standard deviation (SD) one with respect to baseline SD. We based the margins on what might be considered clinically relevant effects given our pilot data. We will use intention-to-treat approaches, comparing randomized arms, with confirmation by per-protocol analyses (i.e. restricting sample to those who properly used the method of disclosure as assigned). We will only declare non-inferiority if both intention-to-treat and per-protocol analyses are consistent, as recommended [133, 134]. For the secondary outcome receipt of results, we will examine non-inferiority of proportions. We will declare non-inferiority if the upper bound of the randomization effect 95% one-sided confidence interval for receipt of results is < 10% in the direction that favors usual care. Since all participants will have the option to speak with a GC, we will conduct secondary as-treated analyses (i.e. based on whether genetic counseling was actually received in both arms).

In secondary analyses, we will use T-tests and Fisher’s exact tests for superiority testing. We will assess balance of potential confounders (e.g. age, race, study site) between arms using T-tests or Fisher’s exact tests. We will use multiple linear regressions (continuous outcomes) and logistic regressions (presence of a behavior such as receipt of results or uptake of confirmation testing) to examine effects after adjusting for potential confounders inadequately balanced. For longitudinal analyses that include all three time points (T0, T1, and T2), we will estimate regressions by Generalized Estimating Equations (GEEs); we will include main and interaction terms between arm and time [135]. 

Intervention costs will be estimated for each study arm, and mean costs per participant will be reported. We will perform a benefit-cost analysis comparing the two study arms, where net benefit (or cost) of the intervention is estimated as the difference in mean downstream costs (i.e., savings in health care expenditures attributable to the intervention) minus the difference in mean intervention costs. In sensitivity analysis, we will vary both intervention cost items and the costs of downstream health care services over reasonable ranges and examine the impact on results. The time horizon of the benefit-cost analysis will be limited to the 12-month follow-period. We will not project longer-term outcomes, nor will we estimate the potential economic impact on family members of genetic test results in study participants, as these are beyond the scope of this study.

#### Sample size justification for aim 1

We chose *n* = 255/arm so we could conclude non-inferiority of digital-ROR if randomization effects comparing the digital arm to GC arms at T1 do not show clinically relevant worsening in the web arm. We chose a margin of -0.45 standard deviation units for knowledge and 0.20 for distress since they are considered modest changes in behavioral research, and they are consistent with our pilot data. In preliminary data from our pilot study, the baseline knowledge standard deviation was 2.86 points. A -0.45 standard deviation difference * (times) 2.86 = -1.29 points. A 1.29 point worsening in the knowledge scale would not be considered a meaningful difference. For disease specific distress, the baseline standard deviation was 9.31 points. A 0.20 standard deviation difference * (times) 9.31 = 1.86 points. Again, a 1.85 unit worsening in the distress scale would not indicate a clinically relevant change.

Table 4 demonstrates potential allowable non-inferiority differences. We chose 2.5% Type I error by applying a Bonferroni correction to a 5% Type I error rate with 2 comparisons (5%/2 = 2.5%). We calculated power using simulations in R with confirmation using PASS 11 software. For our secondary outcome of receipt of results, we will declare digital-ROR effect non-inferior if the upper bound of the 95% one-sided confidence interval effect is less than 11% in a direction that would favor usual care. This has an approximate 5% non-inferiority Type I error rate and > 80% power over a range of plausible differences given our preliminary data (e.g. >55% promising rate seen in preliminary data versus < 44% discouraging rate, *n* = 255/arm). We assumed a binomial pooled standard error estimator. We do not correct for multiple testing of secondary outcomes.

**Table 4 Tab4:** Estimated non-inferiority power, 2.5% Type I error (1-sided), number = 255/group (510 total)

Variable	Biobank Wave 2 Pilot Study	Non-inferiority difference allowed	Non-Inferiority Type 1 Error Rate and Power
Knowledge	T1 Mean 13.20, SD = 2.59 GC arm T1 Mean 12.50, SD = 2.12 Web arm Web minus GC effect = -0.7 Baseline standard deviation = 2.86	-0.45 SD units * 2.86 base SD = -1.29 point margin	2.5% Type I error rate > 80% power with − 0.7 pilot data effect > 99% power with 0 point effect
Disease-specific Distress	T1 Mean 6.22, SD = 5.72 GC arm T1 Mean 6.00, SD = 6.42 Web arm Web minus GC effect: -0.22 Baseline SD = 9.31	0.20 SD units * 9.31 base SD = 1.9 point margin	2.5% Type I error rate > 95% power with − 0.22 pilot data effect > 90% power with 0 point effect.

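### The primary non-inferiority rule labels the wrong confidence bound for knowledge and does not say whose baseline SD turns the margins into points

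*Protocol article*

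**What the plan says.** The section on primary non-inferiority analyses gives one decision rule for two outcomes. For knowledge, non-inferiority is concluded if the "upper bound of the randomization effect 97.5% one-sided confidence interval [CI] for cross-sectional T1 responses do not cross a -0.45 standardized difference threshold". For distress the limit is "a 0.2 standardized threshold (i.e., margin) for disease-specific distress". The sentence ends by saying that crossing is judged on the side on which digital-ROR would be the worse arm. The scale is then defined: "A standardized difference is the difference after variables are scaled to have standard deviation (SD) one with respect to baseline SD". The text does not say whether that SD comes from the pilot or from this trial. It adds that the margins reflect clinically relevant effects in the light of pilot data.

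The sample size justification for Aim 1 multiplies the SD margins by pilot baseline SDs (2.86 for knowledge, 9.31 for distress) and defends the results in points: "A 1.29 point worsening in the knowledge scale would not be considered a meaningful difference", and "a 1.85 unit worsening in the distress scale would not indicate a clinically relevant change". The line before the latter gives the product as 1.86. Table 4 repeats the conversion, for distress as "0.20 SD units * 9.31 base SD = 1.9 point margin". It also reports the pilot effects as web minus GC (-0.7 for knowledge, -0.22 for distress).

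**The concern.** Two things in the rule are not settled by its wording.

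**The bound.** More knowledge is better and more distress is worse, so on a web-minus-GC scale harm is negative for knowledge and positive for distress. A single named bound cannot serve both. Upper is right for distress and wrong for knowledge. If the rule were written as GC minus web, upper would be right for knowledge, but the margin would then be +0.45, and the text has -0.45.

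**The scale.** Scaling variables to an SD of one at baseline reads most naturally as dividing by the SD of the data being analysed. The sample size section, however, treats the margins as fixed point values from the pilot. The two agree only if the trial's baseline SD equals the pilot's. If it does not, there are two possible pass lines and the article does not say which binds.

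This is the success criterion for both primary outcomes. An ambiguity left open until the results are known would have to be resolved with the answer in view.

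**Working it through.** **Inputs.** From Table 4 and the sample size justification for Aim 1: 255 per arm; one-sided alpha 2.5% per outcome (z = 1.96); T1 SDs of 2.59 (GC) and 2.12 (web) for knowledge, and 5.72 and 6.42 for distress; pilot baseline SDs 2.86 and 9.31.

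**Standard errors**, SE = sqrt((SD1² + SD2²)/255):
- Knowledge: sqrt((2.59² + 2.12²)/255) = 0.2096
- Distress: sqrt((5.72² + 6.42²)/255) = 0.5385

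**Point margins:** 0.45 × 2.86 = 1.287; 0.20 × 9.31 = 1.862.

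**Step 1: reproduce the stated power with the bound on the harmful side.** Power = Φ((margin − adverse true difference)/SE − 1.96).
- Knowledge at -0.7: Φ((1.287 − 0.7)/0.2096 − 1.96) = 80.0% (80.4% with 1.29). Stated: above 80%.
- Knowledge at 0: above 99.9%. Stated: above 99%.
- Distress at 0: Φ(1.862/0.5385 − 1.96) = 93.3%. Stated: above 90%.
- Distress at -0.22: Φ((1.862 + 0.22)/0.5385 − 1.96) = 97.2%. Stated: above 95%.

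All four agree. Using the baseline SDs as outcome noise instead gives 64% for knowledge at -0.7, and 62% (at 0) and 71% (at -0.22) for distress, which do not. The planning therefore used the correct side, T1 SDs for noise and point margins from the pilot.

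**Step 2: what the label does if taken literally for knowledge.** With the lower bound, the observed difference must exceed -1.287 + 1.96 × 0.2096 = -0.88 points, and a true difference at the margin passes 2.5% of the time. With the upper bound on web minus GC, observed differences down to -1.287 − 1.96 × 0.2096 = -1.70 points would pass, and a true difference at the margin would pass 97.5% of the time. Step 1 shows that this is not the rule the trial was designed on.

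**Step 3: what the unnamed SD does if it is the trial's own.** The trial's baseline SDs are not in the article, so the values below are assumptions. Outcome SDs are held at the pilot's T1 values.

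| Outcome | Assumed baseline SD | Margin (points) | Power |
|---|---|---|---|
| Knowledge, at -0.7 | 2.0 | 0.90 | 16% |
| | 2.37 | 1.07 | 42% |
| | 2.86 (pilot) | 1.29 | 80% |
| | 3.5 | 1.58 | 99% |
| Distress, at 0 | 6 | 1.20 | 61% |
| | 9.31 (pilot) | 1.86 | 93% |
| | 11 | 2.20 | 98% |

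Worked row: 0.45 × 2.37 = 1.0665, and Φ((1.0665 − 0.7)/0.2096 − 1.96) = 0.416. The value 2.37 is the pooled pilot T1 SD, sqrt((2.59² + 2.12²)/2), used only for illustration.

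**Step 4: sampling error alone.** With 510 people the relative standard error of an SD is about 1/sqrt(2 × 509) = 3.1%. That moves the margins by ±0.08 points (knowledge) and ±0.11 points (distress) at 95%. Simulated type I error at the margin is then 2.7% for knowledge and 2.5% for distress. Only a trial population whose spread truly differs from the pilot's would matter.

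**Step 5: the three distress figures.** Power at no difference is 93.0% for 1.85, 93.3% for 1.862 and 94.2% for 1.9.

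**The case against.** A reader might infer that the pass line points the wrong way and that a digital arm as bad as the margin would nearly always pass. The documents do not support that. The same sentence names the harmful direction. The authors also use upper bound for receipt of results, where more is again better, so it looks like their shorthand for the bound on worsening. The stated power reproduces with the correct side. The 97.5% in Step 2 follows only if the direction clause is ignored. What stands is that the shorthand does not fit a negative margin on a web-minus-GC scale.

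A reader might also infer that the margins are tied to the trial's own SD. The article does not say so. The only baseline SDs it prints are the pilot's, the margins are described as chosen in the light of pilot data, and the SD units have their own justification as modest changes in behavioural research. Which SD enters the computation may be spelled out in an analysis plan not shown here. Under an SD-scaled margin, moreover, a true loss of 1.29 points passing more often is not a type I error, because the null itself has moved. All of this is fair, and it limits the point to an unresolved choice between two readings, with illustrative sizes. It does not remove it, since the article states the rule in one form and justifies it in another.

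The three versions of the distress margin are rounding and a slip of 0.01 points, with no effect on any conclusion. Using T1 SDs for the noise is correct, because the test is on T1 responses.

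**Conclusion.** The point holds as a wording fault in the primary decision rule. That upper is the wrong label for knowledge is certain from the article's own sign convention and margin. It leaves alpha, power and sample size as designed (80.0% and 93.3% at the planning values).

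That the rule fails to name the baseline SD is also certain. Its consequence is conditional: if the pilot's SD applies, nothing changes; if the trial's applies, the point margins and the power move with it. Knowledge has little slack, since power at -0.7 is 80% with the pilot's SD. The sizes in Step 3 rest on assumed baseline SDs and on pilot T1 SDs recurring. They show sensitivity and do not predict what the trial will find.

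**What to change.** Before the final data are opened, restate the rule in points with one value per outcome: digital-ROR is non-inferior on knowledge if the lower one-sided 97.5% bound for digital minus GC is above -1.29 points, and on distress if the upper one-sided 97.5% bound is below 1.86 points. State that these values come from the pilot baseline SDs and are fixed, and that standardized differences are reported descriptively. Use 1.86 wherever the distress margin appears.

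The cost is one paragraph and small edits to the sample size text and Table 4. Both values are already in the article, so alpha, stated power and 255 per arm stand. The downside is that the primary criterion is clarified after the interim analysis, which was done when 200 participants had completed T1. The change should therefore be dated and documented, with the reason given. If the investigators did intend the trial's own SD, moving to points is a change of criterion and should be recorded as one.

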#### Randomization

After at least 4 weeks, participants with an actionable finding (cases) who have not chosen to opt-out of receiving their results are randomized to receive their results by remote telehealth disclosure with a GC (Arm 1) or by a private ROR digital intervention (Digital-ROR) with the option to schedule a call with a GC at any time in the process (Arm 2). A permuted block design is used for randomization, stratifying by cancer or cardiovascular genes and sex.

Randomized participants are sent the Step 2 Letter by MyPennMedicine portal (MPM), encrypted email or mail informing them that an actionable genetic finding that could potentially impact their health has been identified (Supplemental Fig. 2). The letter includes how they will receive their actionable results (according to their randomization), the next steps for receiving results and that they can still elect to NOT receive results. Procedural controls do not receive the Step 2 Letter, but any who opt-out of results after the Step 1 Letter has their decision recorded in case they are found to have an actionable result with additional sequencing or analysis.

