#### Uptake of results and patient reported outcomes (aims 1 and 2)

Theoretically informed patient-reported cognitive, affective and behavioral outcomes of genetic services are collected at baseline (T0), 2–7 days post-disclosure (T1) and at 6 months (T2).

Knowledge of genetic disease (primary non-inferiority outcome) is evaluated at all time points (T0-T2) using an adapted version of the KnowGene Scale, a 16-item scale administered to patients after genetic testing and/or genetic counseling to measure their understanding of the health implications of genetic test results [111]. It includes health implications to oneself as well as relatives. This measure covers penetrance, actionability, limitations of current technology, and monogenic inheritance patterns. Items 3, 5, 13 and 15 were excluded as they are not relevant to return of actionable results. Additionally, 4 items evaluating understanding of the difference between research and clinical testing and utilized in the RESPECT2 study were added to create a final scale of 16 items. This adapted scale has had good internal consistency in our pilot and related studies (Cronbach’s α = 0.63–0.83) [79, 112]. Perceived risk of cancer and cardiovascular disease (T0-T2) is evaluated with a numerical scale (risk 0-100%) and an 5-point verbal scale (much lower than average risk to much higher than average risk) as utilized in our related studies. The 8-item Attitudes Toward Genetic Testing scale is assessed at baseline to understand perceptions of genetic testing and to assess informed choice in combination with genetic knowledge and decisions to proceed with testing, as previously utilized in the multi-dimensional measure of informed choice and our related research (Cronbach’s α = 0.73) [113–115]. *Reactions to genetic information* are assessed with multiple instruments that evaluate psychological distress, adjustment and satisfaction. (a) Disease-specific distress (primary non-inferiority outcome) is measured at all timepoints (T0-T2) using the 8-item version of the Revised Impact of Events Scale (RIES) [94, 116–121], evaluating intrusive and avoidant thoughts regarding cancer and cardiovascular disease separately. The 8 item scale has strong internal consistency in related studies and our pilot study (Cronbach’s α = 0.70–0.92) [122, 123]. (b) *General anxiety and depression* are assessed by the respective 4-item short Patient Reported Outcomes Measurement Information System (PROMIS) scales (Cronbach’s α = 0.88 and 0.86) [79, 124]. (c) *Satisfaction with genetic services* (T1 only) will be assessed with a 14-item satisfaction with communication scale, and adapted for telehealth and digital disclosure, evaluating participants’ experience with high internal consistency in our related studies (Cronbach’s α = 0.73–0.85) [112, 114, 125] (d) *Multidimensional responses to genetic testing*, including positive responses and uncertainty, are assessed at T1 and T2 using the 20 items from the Multi-dimensional Impact of Cancer Risk Assessment Questionnaire (MICRA) with strong internal consistency in our pilot study by subscales (Cronbach’s α = 0.77–0.85) [79, 126]. (e) Decisional regret (T1, T2) is assessed using with the 5-item validated Decision Regret Scale used in genetic studies [127, 128]. This scale has had strong internal consistency in our pilot study (Cronbach’s α = 0.86) [79]. *Use of genetic information* includes uptake of receipt of actionable research results and other health and communication behaviors. (a) *Uptake of research results (secondary non-inferiority outcome)* will be assessed as completion of a remote telehealth disclosure session with a GC (either arm) or as viewing results in digital-ROR (digital arm). Other secondary uptake behaviors include uptake of supplemental digital education (Aim 2a), assessed as completion of pre-disclosure digital education or Chat 1, actively opting-out of receipt of research results after the Step 1 or Step 2 Letter (Aim 2b), completion of confirmation testing, and completion of clinical genetics follow-up, either by documentation in the EHR or self-report by those who are no longer in the local area. (b) Risk reducing behavioral intention (T1 only) and performance (T2) will be assessed with a close-ended and open –ended items given a lack of established measures and the wide range of potential medical management options depending on the individual gene. General health status and risk modifying behaviors (e.g. diet, exercise, tobacco and alcohol use) will be assessed at baseline and at T2 with items utilized in BRFSS and related studies [73, 125, 129]. Additionally, gene-specific medical management or risk reducing screening and interventions will be abstracted from medical records. (c) Communication of genetic test results includes communication intent (T1 only) and performance (T2) assessed using a 3-item measure of intent and communication to assess intent to share genetic test results with health care providers, family members and other third parties utilized in related research [85–87]. 

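### As described, the primary T1 comparison uses neither the baseline scores nor the stratification factors, which costs precision; covariate adjustment of that comparison appears only as a secondary, balance-test-triggered step

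*Protocol article*

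**What the plan says.** All references are to the protocol article.

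- **Primary test.** Primary non-inferiority analyses bases both primary conclusions on the "randomization effect 97.5% one-sided confidence interval [CI] for cross-sectional T1 responses", set against margins scaled to the baseline SD. It names no model and no covariate.
- **Baseline data.** In the section on uptake of results and patient-reported outcomes: "Knowledge of genetic disease (primary non-inferiority outcome) is evaluated at all time points (T0-T2"). Disease-specific distress, asked separately for cancer and cardiovascular disease, is measured at the same three time points.
- **Strata.** Under Randomization: "A permuted block design is used for randomization, stratifying by cancer or cardiovascular genes and sex".
- **Adjustment.** A paragraph introduced as secondary analyses tests the arms for balance with T-tests or Fisher's exact tests, giving age, race and study site as examples. It then uses linear or logistic regression "to examine effects after adjusting for potential confounders inadequately balanced".
- **Other uses of baseline.** T0 is one of three time points in the secondary GEE models. Baseline variables enter the Aim 3 moderator models. The baseline SD scales the margins.

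**The concern.** The baseline value of a scale is often the best available predictor of its follow-up value. Leaving it out of the deciding comparison widens the interval that is held against the margin. Leaving out stratification factors that predict outcome makes the standard error somewhat too large for a design that has already balanced them.

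The stated adjustment rule does not repair this. It is secondary, and it chooses covariates by whether the arms happen to differ. Under randomisation any such difference is due to chance, so the test examines a null hypothesis already known to be true and says nothing about prognostic strength. A strong predictor that happens to balance is left out, and the covariate set cannot be known in advance.

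Knowledge has most to lose, because its power is only about 80% if the pilot difference is the true one. Non-inferiority also requires consistent intention-to-treat and per-protocol results, and the second uses a restricted sample.

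**Working it through.** **Inputs (Sample size justification for aim 1 and Table 4).**
- "number = 255/group (510 total"), that is, 255 per arm.
- One-sided 2.5% per outcome: "We chose 2.5% Type I error by applying a Bonferroni correction to a 5% Type I error rate with 2 comparisons". Hence z = 1.96.
- Knowledge: margin 0.45 × 2.86 = 1.287 points; pilot effect -0.7; "T1 Mean 13.20, SD = 2.59 GC arm T1 Mean 12.50, SD = 2.12 Web arm".
- Distress: margin 0.20 × 9.31 = 1.862 points; pilot effect -0.22; T1 SDs 5.72 (GC) and 6.42 (web).

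**Step 1: reproduce Table 4 with no adjustment.** Power = Φ((margin − true worsening)/SE − 1.96), with SE = √((SD₁² + SD₂²)/255).
- Knowledge SE = √((2.59² + 2.12²)/255) = 0.2096. At -0.7: Φ((1.287 − 0.7)/0.2096 − 1.96) = 79.97% (stated as above 80%). At 0 the power exceeds 99.9% (stated as above 99%).
- Distress SE = √((5.72² + 6.42²)/255) = 0.5385. At -0.22: Φ(2.082/0.5385 − 1.96) = 97.2% (stated as above 95%). At 0: Φ(1.862/0.5385 − 1.96) = 93.3% (stated as above 90%).
- Solving for 80% knowledge power at -0.7 gives 256 per arm, against 255 planned.
- With baseline SDs instead, power would be 64.0% (knowledge, -0.7) and 61.7% (distress, 0). Even at a correlation of 0.6, baseline SDs give only 80.6% for distress at 0, below the stated 90%.

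Table 4 states lower bounds, so these alone do not exclude a baseline gain. The near-exact match on 255 points to raw T1 SDs with none.

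**Step 2: adjust for T0.** ANCOVA multiplies the SE by √(1 − r²), where r is the T0-T1 correlation. The documents do not give r, so it is assumed.

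| r | Knowledge power at -0.7 | Distress power at 0 | Estimate-to-limit distance, knowledge / distress (points) | Adjusted n per arm matching 255 unadjusted |
|---|---|---|---|---|
| 0 | 80.0% | 93.3% | 0.411 / 1.055 | 255 |
| 0.3 | 83.5% | 95.2% | 0.392 / 1.007 | 232 |
| 0.5 | 89.9% | 97.9% | 0.356 / 0.914 | 191 |
| 0.6 | 93.8% | 99.1% | 0.329 / 0.844 | 163 |

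For example, knowledge at r = 0.5: SE = 0.2096 × 0.866 = 0.1815, and Φ(0.587/0.1815 − 1.96) = 89.9%. The last column is 255 × (1 − r²). The table assumes complete T0 and T1 data and takes no credit for the strata.

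**Step 3: the balance-test rule.** A simulation of 40,000 trials per setting, at the non-inferiority boundary, adjusted for T0 only when a baseline t-test gave p < 0.05. At nominal one-sided 2.5%, never adjusting and always adjusting both gave 2.5%. The triggered rule gave 2.2% (r = 0.5) and 1.8% (r = 0.7), so it is conservative. This bears on the secondary regressions only.

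**The case against.** - **The article never says unadjusted.** Cross-sectional may only separate the T1 test from the longitudinal models, and an ANCOVA at T1 is cross-sectional too. A full analysis plan could name covariates, and leaving a baseline gain out of a power calculation is a common conservative choice. This stands as a caution: unadjusted is an inference. It is supported by the absence of any covariate, by the placing of adjustment under secondary analyses, and by Table 4. The article also commits to an adjustment rule, so the point is not only about silence.
- **The balance test cannot change the primary verdict.** This stands. A reader might infer that chance imbalance could decide non-inferiority; the rule is confined to secondary analyses.
- **Other models use baseline data without a balance test.** This stands for the GEE and Aim 3 moderator models. The claim is limited to covariate adjustment of the T1 arm comparison. Chained-equation imputation in the primary analyses might also draw on T0.
- **Nothing is invalid.** This stands. A reader might infer bias or a false-positive risk, but the unadjusted comparison held 2.5% in simulation, and ignoring strata errs on the conservative side. The article gives no figures showing that the strata are prognostic.
- **The gain rests on an assumed correlation.** This stands. The reported Cronbach's alpha for knowledge goes down to 0.63. If reliability were that low at both times, r could hardly exceed 0.63, so 0.6 is near the top of what is plausible. At 0.3 the gains are modest.

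**Conclusion.** The point holds as one of efficiency and pre-specification. As described, the deciding comparison makes no use of baseline scores or strata that the trial already collects. At 255 analysed per arm and r from 0.3 to 0.6, using the T0 score would raise knowledge power at -0.7 from 80% to 84-94%, and distress power at 0 from 93% to 95-99%. This assumes the pilot T1 SDs, the normal approximation and complete data. Any further gain from the strata is unquantified and depends on their being prognostic. The change should be made, chiefly for knowledge, but a positive result from the plan as it stands would not be invalid on this ground.

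**What to change.** - **Primary analysis.** Pre-specify ANCOVA of T1 score on arm, T0 score of the same scale (same disease for distress), gene stratum and sex. Fit it within each imputed data set, for both intention-to-treat and per-protocol. The margins stay as they are, because they are scaled to the baseline SD and the adjusted effect is on the same scale.
- **Timing of T0.** Use only T0 values recorded before the Step 2 Letter and impute the rest. Table 1 places a survey request at the end of pre-disclosure education, and the arm descriptions allow that education to be completed after the letter. Some T0 values may therefore follow news of a finding and of the assigned route. The article does not say how many.
- **Secondary T1 regressions.** Replace the balance-test trigger with a fixed covariate list.

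**Cost.** No new data collection. Missing T0 values need handling, which will reduce the gain somewhat. An interim analysis has already been done on 200 T1 completers and Aim 1 is expected to finish in 2026, so the change must be a dated, documented amendment made before the final unblinded analysis.

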#### Enrollment goals

Our enrollment goal for the primary non-inferiority aim (Aim 1) is 255 participants per arm. To achieve this goal, up to 2500 PMBB participants (cases and procedural controls) are expected to be contacted.

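### The non-inferiority limit for receipt of results is 10% in the analysis section but 11% in the sample size section, and the stated power matches the 11% limit

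*Protocol article*

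**What the plan says.** The protocol article states the decision rule for receipt of results twice.

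- Under *Primary non-inferiority analyses*, non-inferiority is declared if the upper bound of the "95% one-sided confidence interval for receipt of results is < 10% in the direction that favors usual care".
- Under *Sample size justification for aim 1*, digital return is declared non-inferior if the "upper bound of the 95% one-sided confidence interval effect is less than 11% in a direction that would favor usual care".

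The second section then attaches operating characteristics to the 11% rule: "This has an approximate 5% non-inferiority Type I error rate and > 80% power over a range of plausible differences". Its example is a ">55% promising rate seen in preliminary data versus < 44% discouraging rate" at 255 per arm, and it adds: "We assumed a binomial pooled standard error estimator". The sample size agrees with *Enrollment goals*: "Our enrollment goal for the primary non-inferiority aim (Aim 1) is 255 participants per arm". The outcome is secondary, and the article says of such outcomes: "We do not correct for multiple testing of secondary outcomes".

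**The concern.** Outcome, confidence bound and direction are the same in both sections; only the limit differs. Rounding does not explain it, because 55% against 44% is a gap of exactly 11 points. The text is not from a change log and is not damaged by extraction. Nor is it a detail left to a fuller document, since the article states the rule twice, in two forms.

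Two things follow. First, some results would be non-inferior under one section and not under the other. Second, the quoted power belongs to one limit only, so a reader who takes the analysis section as the rule is given power that does not apply to it. Receipt is the only outcome apart from the two co-primaries for which the article gives a margin. The trial has had an interim analysis and expects to complete Aim 1 in 2026, so a margin chosen after the receipt data are known would carry little weight.

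**Working it through.** **Inputs, all from the article:** n = 255 per arm; one-sided 5% (z = 1.645); pooled binomial standard error; planning rates 55% and 44%; limits 10% and 11%. No dropout figure is given for this outcome and none is used.

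**Step 1. Reproduce the plan's own figure (11 points).** Two-proportion formula with pooled variance under the null, 55% against 44%, mean rate 0.495:

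- n = [1.645·√(2·0.495·0.505) + 0.842·√(0.55·0.45 + 0.44·0.56)]² / 0.11² = (1.163 + 0.591)² / 0.0121, which rounds up to 255 per arm.
- Power at 255 per arm: 80.1%.

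As a non-inferiority test with 55% in both arms:

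- SE = √(2·0.55·0.45/255) = 0.0441.
- Power = Φ(0.11/0.0441 − 1.645) = 80.3%; exact binomial enumeration gives 80.1%.
- With true rates of 55% and 44%, the 11% rule passes 4.9% of the time, as the stated error rate of about 5% requires.

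The plan's figures therefore reproduce at 11%.

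**Step 2. Same inputs, 10% limit.**

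- Power = Φ(0.10/0.0441 − 1.645) = 73.4%; exact 73.6%. The two-proportion formula for 55% against 45% gives 73.1%.
- n for 80% power = (1.645 + 0.842)²·2·0.55·0.45/0.10², which rounds up to 307 per arm. It is 310 with both rates at 50%, and 309 by the two-proportion formula for 55% against 45%.

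**Step 3. Where the two rules disagree.** The largest observed deficit that passes is the limit minus 1.645·SE:

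- 10% limit: 0.10 − 0.0725 = 0.0275, about 2.8 points.
- 11% limit: 0.11 − 0.0725 = 0.0375, about 3.8 points.

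**Step 4. Power by true rates, 255 per arm, normal approximation.**

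| GC arm / digital arm | 10% limit | 11% limit |
|---|---|---|
| 50% / 50% | 73.0% | 79.9% |
| 55% / 55% | 73.4% | 80.3% |
| 55% / 54% | 65.4% | 73.3% |
| 55% / 53% | 56.7% | 65.3% |
| 55% / 56% | 80.4% | 86.0% |
| 75% / 75% | 83.2% | 88.9% |

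At the 10% limit, 80% power is reached when both true rates are about 71% or higher, or when the digital arm is truly about 1 point better than a 55% GC rate.

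**The case against.** The best reply is that the calculation is correct for the limit it names. At 11% the sample size, power and error rate all reproduce, so the 10% in the analysis section may be the slip. That stands: this is a contradiction between sections, not an arithmetic error, and it is a reason not to assume that 10% was the intended value. It does not remove the contradiction.

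Four stronger readings are tempting, and the article does not support them.

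- *More than 80% power is attainable only at 11%.* This holds at equal rates of 55%. It fails at higher rates or with a small true advantage for digital return. The planning rate is given as above 55%, and the Background cites uptake of 48% to 86%, though around 50% in biobanks.
- *The claim of "> 80% power over a range of plausible differences given our preliminary data" is false.* At 11%, power is 80% or more when the 55% planning rate holds in the GC arm and the true difference is zero or favours digital return. That is a range, and a plausible one, because the digital arm can receive results online or from a counselor. Lower power under a true deficit is a caution, not a refutation.
- *The 11% rule has inflated error because it passes about 7.8% of the time at a true 10-point deficit.* That tests one rule against the other margin's null. At its own 11-point null the rate is about 5%.
- *The margin was moved after the interim look.* The article ties the interim analysis to completed T1 surveys and does not say that receipt was examined.

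It can also be argued that receipt is measurable in everyone randomised, so the number analysed could exceed 255 per arm if 255 counts survey completers. If, purely as an assumption, 55% complete, 255/0.55 is about 464 per arm, and power at 10% would be about 92%. But the article's receipt calculation uses 255, and two limits would still be in force.

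**Conclusion.** The point holds as an internal contradiction about a secondary outcome. One formal test has two limits, and the stated power and error rate match the 11% limit. At 255 per arm with 55% receipt in both arms, the analysis-section rule has about 73% power against about 80% for the sample-size rule, roughly 7 points lower. The conclusions part for observed deficits of about 2.8 to 3.8 points; this window assumes rates near 55% and 255 analysed per arm. The co-primary tests of knowledge and distress, and their power in Table 4, are untouched. The article alone does not show which limit was pre-specified.

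**What to change.** Before the final data are opened, state one margin in both sections, taken from the dated, pre-specified full protocol. If no dated record supports 11%, the stricter 10% is the conservative choice.

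- If 10% is kept: change the limit in the sample size section and restate power as about 73% at 255 per arm with equal 55% rates.
- If 11% is kept: correct the sentence in the analysis section, and say that the roughly 80% power assumes no true deficit, falling to about 65% with a true 2-point deficit.

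The cost is about one sentence in each section. No change to enrolment or to the primary analyses is needed. Keeping 10% means reporting a less favourable power figure.
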